5.3.9 Blinding

Blinding of the participants will not be feasible, nor is blinding of members of the study team who are actively involved in the administration of the study, or the health economist. However, members of study team responsible for the statistical analysis of the study will be kept blind to group allocation.

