Participants will be prescribed a 30 minute home based foot and ankle exercise programme which should be undertaken three times per week indefinitely. The exercises will be demonstrated by the podiatrist at the participant’s initial visit and will be supplemented by a DVD demonstrating the exercises and an illustrated explanatory booklet showing how to do them at home. The exercise programme which is aimed at stretching and strengthening the muscles of the foot and ankle is based on the programme developed by Spink MJ *et al [22]* and the routine exercises prescribed by podiatrists in the UK.

Participants will complete a questionnaire at 1, 3, 6 and 12 months after randomisation to collect data on compliance with the intervention including the exercise programme footwear advice and insole use, which will be returned to the YTU.

1. Falls prevention leaflet

Participants will receive a copy of the latest falls prevention advice leaflet produced by Age UK. The current version of this document is called “Staying steady. Improving your strength and balance”. This leaflet will be sent to the participant in the post with their baseline questionnaire.

Participants will be sent a site and group specific newsletter at three months and with their six month follow-up questionnaire to inform them about progress with the study. The intervention group’s newsletter will include a section about the foot and ankle exercises in order to aid compliance.

The podiatrist will book a second appointment in approximately two to four weeks time to allow participants sufficient time to purchase new shoes if required. At the second appointment the podiatrist will check the suitability of the new footwear, check that the orthotic device is fitted correctly, customising if necessary. The podiatrist will reinforce the exercise programme. They will ask the participant if they have experienced any adverse events since their last appointment and if they have experienced any problems after undertaking the exercise programme.

It is not anticipated that participants will require a third appointment, however, if participants experience any problems with their orthotic, they will contact the clinic directly to arrange further appointments as required.

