5.4.2 Data collection for the primary outcome for the REFORM Trial

The primary outcome is the rate of falls (ie falls/person/time). A fall is defined as “an unexpected event in which the participant comes to rest on the ground, floor, or lower level”. [31] Data will be collected via participant self-reported falls calendars in the 12 months following randomisation. Participants will be asked to record if they had any fall or not for each day. Participants who do not return their falls calendar within one week of the due date will be telephoned by the YTU, and information collected from the patient over the phone. Participants will also be given the YTU free phone number to ring during office hours to report any fall they have as soon as possible after the fall. The YTU personnel will collect information including: details of the event ie date of event, cause/reason for fall, consequence of fall: superficial wound (bruising, sprain, cut, abrasions) or fractures and type of fracture, footwear worn whilst having the fall, hospital admissions, if the patient was wearing their orthotic at the time of falling or if they were undertaking the prescribed exercises, EQ5D. However, as we are also collecting falls data from the six and 12 month follow up questionnaires, these data will be used for those participants to do not return their monthly falls calendar.

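### The telephone part of falls collection is not masked, and its questions point to the arm, so recording of the primary outcome could differ by arm

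*Protocol*

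**What the plan says.** Section 5.4.2 makes the self-completed calendar the main instrument: "Data will be collected via participant self-reported falls calendars in the 12 months following randomisation". Each day is marked for a fall or no fall.

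The telephone enters in two ways:
- Late calendars: "Participants who do not return their falls calendar within one week of the due date will be telephoned by the YTU", and the information is then taken by voice.
- Self-report: "Participants will also be given the YTU free phone number to ring during office hours to report any fall".

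Trials-unit personnel then collect the details of the event. These include its date, cause and consequences, and also "if the patient was wearing their orthotic at the time of falling or if they were undertaking the prescribed exercises".

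The questionnaires are a further back-up for missing calendars: "as we are also collecting falls data from the six and 12 month follow up questionnaires".

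On masking, section 5.3.9 says that blinding of participants is not feasible, "nor is blinding of members of the study team who are actively involved in the administration of the study". It adds that "members of study team responsible for the statistical analysis of the study will be kept blind to group allocation". Section 5.3.8 has the same trials unit write to participants and their GPs with the allocation.

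In section 5.3.10, the podiatrist sees intervention participants again after about two to four weeks: "They will ask the participant if they have experienced any adverse events since their last appointment". Section 5.3.11 describes no matching visit for controls.

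**The concern.** The outcome is a count of self-reported events in an open trial, so it depends on who asks, how they ask, and whether they know the arm. A caller who knows the arm may prompt harder in one group, or take a vague answer differently. Masking the analysts cannot repair data that were collected differently by arm.

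Participants and treating podiatrists cannot be masked. A member of staff chasing a calendar can be, at least in part, and section 5.3.9 gives this up along with the rest. Even a caller who starts out unaware of the arm may learn it from the orthotic and exercise questions, and may call the same person again in later months.

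At stake are the estimated rate ratio and its credibility. A reader of the results could not tell how much of a difference arose in the telephone component.

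**Working it through.** **Setting the sections side by side**

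1. *Does the telephone supply outcome data?* Yes. Section 5.4.2 uses it for late calendars and for self-report. Section 5.4.6 names the telephone notification form, with the calendar and the questionnaire, as a source for the date of first fall.
2. *Are the callers masked?* The protocol does not say in so many words that they know the arm. It follows by inference: they belong to the unit that issues allocations (5.3.8), administering staff are unblinded, and only analysts are masked (5.3.9). No masked call handling is described.
3. *Do the questions point to the arm?* The exercise item clearly does, because exercises are prescribed in one arm only. The orthotic item does so less clearly. Wearers of existing orthotics are not excluded, and controls continue their current podiatry care, so a control may own one.
4. *Do the arm-revealing items decide whether a fall counts?* No. They describe a fall already reported. Any effect on the count would act through prompting, vague or borderline reports, or later calls to the same person.

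**Size: illustration only**

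The documents give neither the telephone share of falls nor any difference in recording. Both are assumptions here.

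Let *s* be the share of falls obtained by telephone and *d* the proportion of those under-recorded in the intervention arm relative to control. The observed rate ratio is the true one × (1 − *s·d*).

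| *s* | *d* | multiplier | true 1.00 reads | true 0.80 reads |
|---|---|---|---|---|
| 0.20 | 0.10 | 1 − 0.02 = 0.98 | 0.98 | 0.78 |
| 0.40 | 0.10 | 1 − 0.04 = 0.96 | 0.96 | 0.77 |
| 0.20 | 0.20 | 1 − 0.04 = 0.96 | 0.96 | 0.77 |
| 0.40 | 0.20 | 1 − 0.08 = 0.92 | 0.92 | 0.74 |

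If the difference ran the other way, the multipliers would be 1.02 to 1.08.

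**What a shift of this order does to a test**

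The planning figures in section 5.3.6 are for the proportion of fallers: 50% against 40%, 80% power, two-sided 5%, 445 per arm, 10% loss.

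- *Check of the plan's figure.* The usual two-proportion formula gives 388 per arm; 388/0.9 rounds up to 432, a total of 864. With continuity correction it gives 408 per arm; 408/0.9 rounds up to 454, a total of 908. The stated 890 lies between the two, within 3% of each. Evaluable per arm: 445 × 0.9 ≈ 400, with power 81.3%. The sample size is not in question.
- *Formula.* With *n* = 400 per arm, observed proportions p₁ and p₂, and mean p̄: SE₀ = √(2p̄(1−p̄)/n), SE₁ = √((p₁(1−p₁)+p₂(1−p₂))/n). P(reject) = 1 − Φ((1.96·SE₀ − (p₁−p₂))/SE₁) + Φ((−1.96·SE₀ − (p₁−p₂))/SE₁).
- *No true effect, 50% in both arms.* If intervention-arm fallers are captured at 98%, 95% or 90% of the control rate, the apparent differences are 1.0, 2.5 and 5.0 points. The test rejects in about 5.9%, 10.9% and 29% of trials. For the 95% case, p₂ = 0.475, SE₀ = 0.03534 and SE₁ = 0.03533, which gives 0.109.
- *True 50% against 40%.* If intervention-arm capture is 5% or 10% higher than control, the observed intervention proportions are 42% and 44%. Power falls from 81% to about 62% and 40%.

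Two cautions apply. The 90% case goes beyond the table above: at a 40% telephone share it needs *d* = 0.10/0.40 = 25%. And the planned primary analysis is of counts. A person with several falls stays a faller if one is missed, so a given loss of falls shifts faller status by less.

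**The case against.** The case against is substantial.

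- A reader might infer that falls are collected mainly by telephone. They are not. The calendar is primary, and the telephone is a back-up described for all participants without distinction by arm. This objection stands.
- A reader might infer that callers judge whether a trip or slip meets the fall definition. No section gives them that task. The participant reports the fall and staff take down the details. This also stands.
- A reader might infer that the second podiatry visit is an extra route into the primary count in one arm. Sections 5.4.2 and 5.4.6 name only calendar, telephone and questionnaire, and the visit's question concerns adverse events. What remains is narrower. A fall is a listed expected adverse event, and nothing expressly keeps a fall learned only at that visit out of the count. Section 5.3.13 is also unclear: one paragraph has details of any adverse event reported to the unit recorded, and the next says that non-serious ones are not.
- The trial is openly declared unblinded and participants report their own falls. Masked callers would leave that exposure untouched. This is true, but it is no reason to leave a second, reducible exposure in place.
- Call scripts and database permissions may sit in the unit's operating procedures, which are not at hand. That is possible. But the protocol itself addresses blinding in section 5.3.9, and it exempts all administering staff without separating out those who take outcome data.

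**Conclusion.** The point holds in limited form. The telephone components of falls collection have no stated protection from knowledge of the arm, and the event questions, above all the one on prescribed exercises, point to it. Recording that differs by arm is possible, and the protocol as written does nothing to limit it.

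This is a weakness of design that can be reduced cheaply. It is not a contradiction, and it is not evidence that bias will occur. That callers know the arm is an inference from sections 5.3.8 and 5.3.9.

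The size is unknown. The 2–8% shift in the rate ratio rests wholly on an assumed telephone share of 20–40% and an assumed difference of 10–20%. A reader might conclude that the bias favours the intervention. The documents do not support that: caller expectation could push one way and more frequent enquiry in the intervention arm the other, and no net sign can be given.

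**What to change.** Amend sections 5.3.9 and 5.4.2 as follows.

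1. Calendar-chasing and fall-report calls are handled, where possible, from a database view that hides allocation, by existing staff who do not process allocation letters.
2. One script serves both arms. It records and closes the number and dates of falls before any footwear, orthotic or exercise question, and those questions are worded neutrally for everyone.
3. The source of each fall is stored, so that a sensitivity analysis can use calendar-reported falls only.
4. The primary count uses only the calendar, telephone and questionnaire sources already named in sections 5.4.2 and 5.4.6. A fall learned only at the intervention-arm podiatry visit is not counted.
5. The two statements in section 5.3.13 on recording non-serious adverse events are reconciled, so that it is clear what happens to such a fall.

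The cost is a database permission, a reordered script, a source field and a few sentences of text. No new staff or visits are needed, and the sample size is unchanged. The downside is that masking will be partial, since participants may reveal their arm in conversation, and their own reporting bias stays as it is.

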5.4.3 Data collection for secondary outcomes and process data for the REFORM Trial

Patient self-reported data from monthly falls calendars, monthly exercise calendars and follow-up questionnaires will be used to capture the following data:

- Proportion of fallers
- Proportion of multiple fallers
- Proportion of single fallers
- Participant self-reported time to first fall during follow-up over the 12 month follow-up period
- Health related quality of life as measured by the EQ-5D
- Short Falls Efficacy Scale
- Fear of falling
- Activity of Daily Living
- Fracture rate
- Health service utilisation data
- Geriatric depressions scale

5.4.4 Statistical analysis

There will be one single analysis at the end of the trial. All analysis will be conducted using STATA, (StataCorp, version 10.1, 4905 Lakeway Drive, College Station, Texas 77845 USA) and SAS (SAS Proprietary Software version 9.2, SAS Institute Inc., Cary, NC, USA) All analyses will be conducted on an intention to treat basis, ie including all randomised patients in the groups to which they were assigned. If more than 890 participants are recruited and unequal allocation is utilised then analyses will be adjusted to take this into account. The trial statistician and health economist will write detailed analysis plans, based on the protocol after it has been approved.

5.4.5 Statistical analysis of the primary outcome

The number of falls per person will be analysed using a Poisson regression model adjusting for gender, age and history of falling to estimate the difference in falls rate between the groups. If there is over dispersion a negative binomial regression model adjusting for the same factors will be used [41] Point estimates and their associated 95% confidence intervals will be provided. For the main outcome a significance level of 0.05 will be used.

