5.3.4. Primary outcome

The primary outcome is the rate of falls (i.e: falls/person/time) where a fall is defined as “an unexpected event in which the participant comes to rest on the ground, floor, or lower level”. [31]

5.3 5 Secondary outcome

Secondary outcomes are:

- Proportion of fallers
- Proportion of multiple fallers (more than two falls)
- Patient reported time to first fall during follow-up
- Health related quality of life as measured by the EQ-5D
- Short Falls Efficacy Scale
- Fear of falling
- Activity of Daily Living
- Fracture rate
- Health service utilisation
- Geriatric Depressions Scale

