5.3.6 Sample size

This trial is designed to detect a 10% point reduction in the falls over 12 months. Assuming this high risk group have an underlying risk of 50% (the incidence observed in our recent trial of occupational Therapy for falls reduction) then in order to observe a reduction to 40% with 80% power and a two-sided 5% significance level would require 890 participants (445 in each group, allowing for a 10% loss to follow up). However, we propose to recruit 2,600 participants in to the REFORM cohort to allow us to sample for the feasibility phase and to allow cohort attrition before we sample for the main trial. If more than 890 participants are eligible for the REFORM trial we will recruit these and use unequal allocation, which will allow us to maintain the same size intervention group but increase the size of the control group and increase the power of the study.

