5.3.8 Randomisation

Participants who fulfil the eligibility criteria and who have provided written consent to take part in the reform study will be eligible for randomisation into the REFORM trial. The randomisation will be carried out by the York Trials Unit Randomisation Service once all relevant data are collected and entered into the study database. Participants will be randomly allocated in a 1:1 ratio to either the intervention or control group. If more than 890 eligible participants are recruited then we will randomly allocate the remaining participants in a 2:1 ratio in favour of the control group. In order to allow for manageable case loads at individual sites, the randomisation will be blocked and stratified by centre with the allocation sequence being computer generated. Participants will be randomised in batches, the frequency of which will be determined by the capacity of the site delivering the intervention. The York Trials Unit (YTU) will write to participants and their GP’s informing them about their group allocation. The podiatrists delivering the intervention will be notified that a new participant has been randomised to the intervention group via email, telephone call or letter. The podiatrist will then access a secure website to retrieve details of the participant and will arrange the required appointments for that participant.

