**5.4 Data collection and analysis**

5.4.1 Quantitative data collection

Participant self-reported data will be collected at the following time points: at invitation, baseline (pre-randomisation/pre-assessment), monthly falls calendars and at six and 12 months post-randomisation/post-assessment for trial and cohort participants. Data on compliance to the intervention will be collected via questionnaire sent at 1, 3 6 and 12 months. For data collected post-randomisation/post assessment an option to complete the data on-line will be offered.

Follow-up questionnaires will be sent to participants in the post by the research team based at the University of York’s Trials Unit. Participants who provide an email address will be sent a pre-notification email, two weeks prior to the questionnaire being sent in the post. This email will alert participants that they will soon receive a follow-up questionnaire and that they can, if they prefer, complete the questionnaire on-line. Participants who do not return their follow-up questionnaire within two weeks will be sent up to two reminders, two weeks apart either by post, text or email. Members of the research team may also contact participants by telephone, post or email or text as per the participant’s preference regarding any queries they may have in relation to the follow-up questionnaires, exercise diaries or falls calendars. All participants will be sent an unconditional £5 with the 12 month questionnaire in recognition of their commitment to the study and to cover any expenses incurred in completing the questionnaires. When a participant has been lost to follow-up, their data will be included in the main analysis up to where they have been lost to follow-up.

Process data collected via the podiatrists will be collected at the patient’s initial and follow-up attendance to the podiatry clinic. Additional data will be collected if the participant attends additional trial appointments. Attendance to the podiatry clinic by the control participants and details of the treatment/advice given will be recorded.

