5.4.6 Statistical analysis of secondary outcomes

The proportion of fallers versus non-fallers in each group will be compared by logistic regression adjusting for gender, age, centre and history of falling. Odds ratios and their associated 95% confidence intervals will be provided.

The proportion of multiple fallers versus single or non-fallers in each group will be compared over the 12 month trial period using logistic regression adjusting for gender, age, centre and history of falling.

The time to the first fall will be derived as the number of days from randomisation until the patient reports having a fall as detailed from the participant’s falls calendar, telephone notification form or self-reported questionnaire. Participants who have not had a fall will be treated as censored at their date of trial exit, or date of last available assessment or 365 days/trial cessation, as appropriate.

The proportion of patients yet to experience a fall between the two groups will be summarised by a Kaplan Meier survival curve. The risk of experiencing a fall between the two groups during follow up will be analysed by Cox Proportional Hazard regression adjusting for gender, age, centre and history of falling. Hazard ratios and their associated 95% confidence intervals will be provided. The proportional hazard assumption will be evaluated using Schoenfeld residuals. The median time to the first fall and its associated 95% confidence intervals will be estimated from this adjusted model.

The proportion of people with depression in each group will be compared over the 12 month trial period using logistic regression adjusting for gender, age, centre and history of falling.

The following secondary outcomes, Short Fall Efficacy Scale, Fear of falling and Activity of Daily living, Geriatric Depression Scale are continuous and will be measured at baseline, month 6 and month 12. Linear mixed models will be used to compare the two groups on these outcomes adjusting for gender, age and history of falling. Random intercepts for each patient will be included in the models. Model effects and their associated 95% confidence intervals will be provided.

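### The primary falls model omits centre, the randomisation stratifier, although several secondary models include it

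*Protocol*

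**What the plan says.** Protocol 5.3.8 states that "the randomisation will be blocked and stratified by centre with the allocation sequence being computer generated".

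For the primary outcome, 5.4.5 states that "The number of falls per person will be analysed using a Poisson regression model adjusting for gender, age and history of falling". If there is overdispersion, a negative binomial model with the same factors replaces it. Centre is in neither.

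Section 5.4.6 treats the same falls data differently: "The proportion of fallers versus non-fallers in each group will be compared by logistic regression adjusting for gender, age, centre and history of falling". The models for multiple fallers, time to first fall (Cox) and depression carry the same four covariates. The linear mixed models and the fracture GEE in that section go back to gender, age and history of falling.

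Two other places bear on the point. Sections 5.3.6 and 5.3.8 allow recruitment beyond 890, with the extra participants allocated 2:1 in favour of control. Section 5.4.4 says analyses will then be adjusted for this, without saying how, and that the detailed analysis plans will be built on the protocol.

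On exposure, 5.3.4 says "The primary outcome is the rate of falls (i.e: falls/person/time"), and 5.4.1 says of people lost to follow-up that "their data will be included in the main analysis up to where they have been lost to follow-up". Section 5.4.5 models a count per person, with the stated aim of estimating a difference in falls rate. It neither names nor excludes an offset.

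**The concern.** When allocation is balanced within centres, an analysis that ignores centre leaves between-centre variation in the error term. The estimate already benefits from the balance, but the reported standard error does not, so confidence intervals come out too wide and the test is conservative. Some of the planned power is given away.

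The protocol is also inconsistent with itself. Fallers, multiple fallers and time to first fall are analysed with centre, and the primary rate of falls without it, with no reason given. Because 5.4.5 fixes the covariate list, this is not a detail left open. An analysis plan that follows the protocol would inherit the omission.

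A 2:1 stage would raise a second issue. Sites were added by amendment, the Summary allows more to be opened, and 5.3.8 randomises in batches set by site capacity. Late recruits, over-represented in the control arm, could therefore come from centres with different fall rates.

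**Working it through.** **1. The plan's own figure.** Section 5.3.6 says that the design "with 80% power and a two-sided 5% significance level would require 890 participants", for 50% versus 40% fallers and 10% loss. With z = 1.960 and 0.842:

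n per arm = [1.960 × √(2 × 0.45 × 0.55) + 0.842 × √(0.25 + 0.24)]² / 0.10² = 388 rounded up

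388/0.9 gives 432 per arm, 864 in total. With continuity correction it is 408, then 454 per arm, 908 in total. The stated 890 lies between the two, and 400 evaluable per arm gives 81.3% power. The figure reproduces, and adding centre does not change it.

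**2. Standard error with and without centre, 1:1 allocation, no true effect.** The protocol gives no between-centre variation, fall rate or dispersion, so all three are assumed. Eighteen centres matches the eighteen areas in the Summary. Two sets of simulated negative binomial data, mean 1 fall per year:

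| Set | Between-centre SD of log rate | SE without centre | SE with centre | Ratio |
|---|---|---|---|---|
| A: 18 × 44, dispersion 0.9, 300 runs | 0.2 | 0.0993 | 0.0977 | 1.016 |
| A | 0.3 | 0.1022 | 0.0988 | 1.034 |
| A | 0.5 | 0.1099 | 0.1003 | 1.096 |
| B: 890 participants, dispersion 1, 400 runs | 0 | 0.0947 | 0.0938 | 1.010 |
| B | 0.2 | 0.0967 | 0.0945 | 1.023 |
| B | 0.4 | 0.1021 | 0.0958 | 1.066 |

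In set B about 1% of the excess appears even with no centre variation, so the figure at SD 0.2 is if anything generous. Set B's models held treatment alone or treatment plus centre.

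**3. True variability.** In set B at SD 0.4 the empirical SD of the log rate ratio was 0.0964 without centre and 0.0968 with it. The estimator hardly changes; only its reported standard error does. The rejection rate under no effect was 0.037 without centre and 0.052 with it (nominal 0.05, Monte Carlo error √(0.05 × 0.95/400) = 0.011).

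**4. Power.** Take 80% power with centre in the model, and a true sampling SD equal to the adjusted standard error. Power without centre is then Φ(2.80 − 1.96 × ratio):

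- ratio 1.016: Φ(0.81) = 79%
- ratio 1.034: Φ(0.77) = 78%
- ratio 1.096: Φ(0.65) = 74%

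The loss is about 1, 2 and 6 points. Set B at a rate ratio of 0.8 gave rejection rates without and with centre of 0.635 and 0.630 (SD 0.2) and of 0.588 and 0.615 (SD 0.4). With a Monte Carlo error near 0.025, that is compatible with a small loss.

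**5. The 2:1 stage.** All inputs here are assumed: 890 participants at 1:1 with 1 fall per year, then 150 at 2:1 from centres with 1.5 falls per year, and no treatment effect.

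- Intervention: (445 × 1 + 50 × 1.5)/495 = 520/495 = 1.051
- Control: (445 × 1 + 100 × 1.5)/545 = 595/545 = 1.092
- Crude ratio: 1.051/1.092 = 0.96

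If the late centres had lower rates, the ratio would move the other way.

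**6. Follow-up time, only if no offset were used.** The count ratio equals the true rate ratio times the ratio of mean follow-up. Assume those lost leave on average at mid-year:

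| Lost, intervention v control (assumed) | Mean follow-up, years | Ratio when the true value is 1.00 |
|---|---|---|
| 10% v 10% | 0.950 / 0.950 | 1.00 |
| 10% v 5% | 0.950 / 0.975 | 0.974 |
| 15% v 5% | 0.925 / 0.975 | 0.949 |
| 5% v 15% | 0.975 / 0.925 | 1.054 |

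**The case against.** The strongest reply is that the effect is small and in the safe direction. Under 1:1 stratified allocation the estimate is not biased, type I error is not inflated, and the larger power loss needs the most extreme centre variation assumed. All of that stands. It limits the severity, but it does not explain why the primary analysis alone among the main falls analyses should drop the stratifier.

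On the 2:1 stage, the reply is that it happens only if more than 890 eligible participants are recruited, that the protocol gives no schedule of site openings, and that 5.4.4 already promises an adjustment. This also stands: a different centre mix is possible, not certain. What remains is that the promised adjustment is unnamed and that 5.4.5 contains no term that could deliver it.

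On follow-up time, a reader might infer that the primary model has no person-time term, so that unequal loss would show up as a treatment effect. The protocol does not support that. The outcome is defined per unit of time, 5.4.5 aims at a falls rate, no offset is excluded, and an offset is a detail that an analysis plan, not shown here, would normally supply. The protocol gives 10% loss overall and nothing by arm, so neither the size nor the direction of any imbalance is known. Telephone contact when a calendar is a week late, backfill from the 6- and 12-month questionnaires (5.4.2), and continued follow-up after withdrawal from the intervention only (5.3.7) would all reduce it.

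**Conclusion.** The point holds for centre. The primary model and its fallback, the mixed models and the fracture GEE omit the factor on which randomisation is stratified, while four secondary models include it. The consequence under 1:1 allocation is a reported standard error that is 1.6% to 9.6% too large for an assumed between-centre SD of 0.2 to 0.5. Carrying the protocol's 80% power over to the rate comparison is a further assumption.

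A reader might infer that the rate ratio itself is biased or materially less precise. Under 1:1 allocation it is not: its true variability is almost unchanged, and only the model-based standard error suffers. Confounding by centre becomes possible only if the 2:1 stage is used and the centre mix shifts.

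The offset is a clarification, not an error in the plan. This should be fixed, but it does not threaten the validity of the trial.

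**What to change.** In 5.4.5, add centre to the Poisson model and to the negative binomial fallback, as a fixed effect or, where centres are small, pooled or as a random effect. Add centre to the linear mixed models and the fracture GEE in 5.4.6. The GEE has no random centre effect to fall back on and fractures may be few, so allow small centres to be pooled there.

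State in 5.4.4 what the adjustment for unequal allocation is: if the 2:1 stage is used, include allocation stage (before or after the change of ratio) as well as centre, because centre alone does not separate the stages where a centre recruits in both.

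As a clarification, name the log of observed follow-up time from randomisation as the offset in 5.4.5.

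The cost is wording only, to be agreed before outcome data are seen by arm. Eighteen centres add 17 parameters, against about 801 evaluable participants (890 × 0.9). No stated sample size changes.
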